## Abstract

**Background:**

The incidence of acute kidney injury (AKI) is estimated at 10 to 20% in patients admitted to intensive care units (ICU) and often requires renal replacement therapy (RRT). ICU mortality in AKI patients can exceed 50%. Venous catheters are the preferred vascular access method for AKI patients requiring RRT, but carry a risk of catheter thrombosis or infection. Catheter lock solutions are commonly used to prevent such complications. Heparin and citrate locks are both widely used for tunneled, long-term catheters, but few studies have compared citrate versus heparin for patients with short-term, non-tunneled catheters. We aim to compare citrate 4% catheter lock solution versus heparin in terms of event-free survival of the first non-tunneled hemodialysis catheter inserted in ICU patients with AKI requiring RRT. Secondary objectives are the rate of fibrinolysis, incidence of catheter thrombosis and catheter-related infection per 1,000 catheter days, length of stay in ICU and in-hospital and 28-day mortality.

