**Methods/Design:**

The VERROU-REA study is a randomized, prospective, multicenter, double-blind, parallel-group, controlled superiority study carried out in the medical, surgical and nephrological ICUs of two large university hospitals in eastern France. A catheter lock solution composed of trisodium citrate at 4% will be compared to unfractionated heparin at a concentration of 5,000 IU/mL. All consecutive adult patients with AKI requiring extracorporeal RRT, and in whom a first non-tunneled catheter is to be inserted by the jugular or femoral approach, will be eligible. Catheters inserted by the subclavian approach, patients with acute liver failure, thrombopenia or contraindication to systemic anticoagulation will be excluded. Patients will be followed up daily in accordance with standard practices for RRT until death or discharge.

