## Background

The incidence of acute kidney injury (AKI) varies according to the populations studied and the definition used, but it is estimated to be around 10 to 20% in patients admitted to the intensive care unit (ICU) [1–3]. The cause of AKI is most commonly acute tubular necrosis occurring in the context of shock (septic and/or cardiogenic), or drug toxicities (such as aminoglycosides or contrast medium). The pathophysiology of AKI is well established, and includes vascular, medullar and tubular injury leading to a reduction in the rate of glomerular filtration, and ultimately, anuria [4]. Renal replacement therapy (RRT) can be required, depending on the AKI etiology and comorbidities, particularly pre-existing renal insufficiency. In one observational study carried out among almost 30,000 ICU patients, the rate of RRT was around 4% [3], but rates as high as 70 to 80% have been reported in patients with shock [5–7]. Mortality in the ICU ranges from 15 to 25%, but can reach 50 to 60% in patients with AKI [3, 8].

Venous catheters are currently the preferred vascular access method for patients with AKI requiring extracorporeal RRT [9, 10]. In critical care, non-tunneled catheters represent standard practice. Despite the vast progress in the management of AKI and high-quality catheter practices [11–13], vascular access remains the weak link in the chain of RRT and contributes to increased morbidity in hemodialysis patients, particularly through catheter dysfunction (stenosis and/or thrombosis) and infection.

Strategies to prevent hemodialysis catheter dysfunction and infection include catheter locks, which are generally either heparin or citrate. The principle of the catheter lock is to instil an anticoagulant solution into the lumen of the branches of the hemodialysis catheter after each RRT session, leaving them in place until the next session.

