#### Secondary endpoints

Secondary endpoints are: the rate of fibrinolysis per 1,000 catheter days, the incidence of catheter dysfunction per 1,000 catheter days, the incidence of catheter-related infection per 1,000 catheter days, the number of hemorrhagic events requiring the transfusion of at least two units of packed red blood cells, length of stay in intensive or critical care, length of hospital stay and in-hospital and 28-day mortality rate.

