#### Primary objective

The primary analysis will be on an intention-to-treat basis. Event-free catheter survival will be compared between groups using the log rank test. Time zero is defined as the time of randomization, and the time to withdrawal of the first non-tunneled hemodialysis catheter (event-free catheter survival) will be calculated starting from randomization for the analysis of the primary endpoint. Patients will be censored in case of scheduled withdrawal of the catheter, or death. Then, multiple Cox regression analysis will be performed as appropriate, to take into account any potential imbalances in potential confounders between groups. Treatment effects will be expressed as HRs with 95% CI. *P* values will also be provided. A per-protocol analysis will also be performed, using the same techniques. For the per-protocol analysis, patients will be grouped according to the treatment actually received.

An interim analysis is planned once 50% of the expected number of patients has been included (after inclusion of 200 patients). The time between randomization and withdrawal of the catheter will be described in both groups and compared using the log rank test, with an alpha risk fixed at 0.0001 (according to the method proposed by Peto *et al*. [42], to avoid inflating the alpha risk of the main analysis at the end of the study).

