#### Secondary objectives

Secondary endpoints will be compared using the chi square test, Fisher’s exact test, Student’s t-test, or the Mann-Whitney U test, as appropriate. Treatment effects will be presented with 95% CI. All analysis will be performed using SAS version 9.2 (SAS Institute Inc., Cary, North Carolina, United States).

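### ICU and hospital length of stay are compared with t or Mann-Whitney tests that cannot tell a stay ended by death from one ended by discharge, so a mortality difference between arms would distort both comparisons

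*Protocol article*

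**What the plan says.** Under Secondary endpoints, the protocol article lists "length of stay in intensive or critical care, length of hospital stay", and closes the list with mortality in hospital and at 28 days. It gives no rule for how a patient who dies enters either length of stay.

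Under Statistical analysis, Secondary objectives, one sentence covers every secondary endpoint: "Secondary endpoints will be compared using the chi square test", Fisher's exact test, Student's t-test "or the Mann-Whitney U test, as appropriate". For a duration, only the last two can apply.

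The abstract (Methods/Design) sets the end of follow-up: "Patients will be followed up daily in accordance with standard practices for RRT until death or discharge". The only rule for death is in the primary analysis: "Patients will be censored in case of scheduled withdrawal of the catheter, or death". It concerns catheter survival and is not extended to length of stay. The Background section says that ICU mortality "can reach 50 to 60% in patients with AKI".

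**The concern.** Death cuts length of stay short. Neither a t-test nor a Mann-Whitney test on observed durations knows why a stay ended, so a death on day 3 ranks ahead of a discharge alive on day 20. In a population where death may be a common end to a stay, the result mixes two things: how long patients need care, and how many die early.

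At stake is the direction of the reading. If one lock were associated with more deaths, and those deaths came early, it could be reported with a shorter stay. A lock with fewer deaths could be reported with a longer one. Restricting the comparison to survivors does not solve this, because survival is itself a post-randomization outcome and the two surviving groups need no longer be comparable.

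**Working it through.** The plan states no figure for length of stay, so there is none to reproduce. The check asks how far the Mann-Whitney test moves when only mortality differs.

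**Inputs from the article:** 193 patients per group (Sample size calculation) and mortality around 50 to 60% at the upper end (Background).

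**Assumptions, not from the article:** lognormal stays with log-SD 0.7; median stay 7 or 12 days in those who die and 12 or 18 days in survivors; the same stay distribution in both arms within each vital-status group; two-sided 5% test.

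**Formula.** Let arm A have mortality mA and arm B mB. Let θ be the probability that a patient who dies has a shorter stay than a survivor. Summing over the four combinations of vital status:

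P(stay A < stay B) = ½·mA·mB + θ·mA(1−mB) + (1−θ)·(1−mA)mB + ½·(1−mA)(1−mB) = ½ + (mA−mB)(θ−½).

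The shift away from ½ is therefore the mortality *difference* times (θ−½). It is zero when mortality is equal, however high, and zero when deaths and survivors stay equally long (θ = ½).

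**Numbers.** For lognormal stays, θ = Φ(ln(survivor median / death median) / (0.7·√2)). With medians of 7 and 18 days, θ = Φ(0.944/0.990) = 0.830. The null standard error is √((2·193+1)/(12·193²)) = 0.0294. For 60% v 50%, the shift is 0.10 × 0.330 = 0.033 and z = 0.033/0.0294 = 1.12. The rejection probability is Φ(1.12−1.96) + Φ(−1.12−1.96) ≈ 0.20. Other cases in the same way:

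| Mortality | Median stay, deaths / survivors (days) | θ | z | Rejection |
|---|---|---|---|---|
| 50 v 50% | 7 / 18 | 0.830 | 0 | 5% |
| 52 v 50% | 7 / 18 | 0.830 | 0.22 | 5.6% |
| 55 v 50% | 7 / 18 | 0.830 | 0.56 | 8.7% |
| 60 v 50% | 12 / 18 | 0.659 | 0.54 | 8.4% |
| 60 v 50% | 7 / 12 | 0.707 | 0.70 | 10.8% |
| 60 v 50% | 7 / 18 | 0.830 | 1.12 | 20% |
| 55 v 50% | 12 / 18 | 0.659 | 0.27 | 5.8% |

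Simulation agrees: 5.4%, 5.3%, 9.0%, 8.8%, 11% and 19 to 20% for the first six rows, and about 6% for the last. In the 60% v 50% case with 7 and 18 days, the higher-mortality arm's median stay comes out about 1.1 days shorter.

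**Sensitivity.** A separate simulation used log-SD 0.8, a survivor median of 15 days and death medians of 8, 5 or 3 days. With 60% v 50% mortality, the higher-mortality arm had a significantly shorter stay in 11%, 21% and 30% of runs by Mann-Whitney and in 8%, 13% and 21% by t-test, against 2.5% nominal in that direction. With equal mortality the share was 2 to 3%.

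**Effect of the remedy.** In that simulation, when deaths took the worst rank, the higher-mortality arm looked significantly better in at most 0.3% of runs in every scenario with unequal mortality.

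**The case against.** The strongest reply is that the article does not say that deaths enter at their observed stay. It names the endpoints and offers a menu of tests. A Mann-Whitney test is compatible with worst-rank scoring, and a derivation rule may sit in a full protocol or analysis plan that is not shown. This stands in part: if such a rule exists, the Mann-Whitney route is sound. But plain two-sample tests, together with follow-up that ends at death or discharge, lead most directly to observed stays. The listed tests also leave no room for a competing-event analysis.

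A reader might infer that mortality above 50% drives the comparison by itself. The documents do not support that. The figure is an upper-end background value, not the rate expected in this trial, and the formula shows that only a difference between arms matters. Nor does the article give any reason to expect a 10-point mortality effect from a catheter lock, since its hypothesis concerns catheter dysfunction. The 20% result is one assumed scenario at the upper end of the table.

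A reader might also infer that the endpoint cannot be interpreted at all. That is too strong. In-hospital and 28-day mortality stand beside it in the same list. In the 60% v 50% scenario with stays of 7 and 18 days, the mortality test was significant in about 49% of simulated trials. Where stay was significant, mortality was too in about 79%. Observed stay also remains readable as bed use. Still, separate reporting of mortality does not correct the p-value or interval for stay, and in about a fifth of those trials the mortality test would give no warning.

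**Conclusion.** The point holds in a limited form. Applied to observed stays, the listed tests treat an early death as a short stay. They favour the higher-mortality arm when two conditions meet: mortality differs between arms, and those who die have shorter stays. Without a mortality difference there is no between-arm bias.

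Under the assumed stays, a 5- to 10-point difference raises two-sided rejection from 5% to about 8 to 20%; it stays near 6% when a 5-point difference coincides with the smaller stay gaps. These sizes rest on assumed stay distributions, because the article gives none, and shorter stays among deaths would make them larger. Severity is minor to moderate: two secondary endpoints are affected, the primary endpoint is untouched, and mortality is reported separately.

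**What to change.** Before unblinding, keep both endpoints and state how death enters their analysis. Either of these would do:

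- analyse time to discharge alive (from the ICU and from hospital) with death as a competing event, shown as cumulative incidence by arm; or
- keep the Mann-Whitney test and give every in-hospital death (in-unit death for ICU stay) the worst rank.

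In both cases, report observed stay descriptively by vital status, next to the mortality results, without a survivors-only significance test.

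The cost is a change of analysis wording. Stay lengths and vital status at the end of the stay are already needed for the listed endpoints. The downside is that the result combines stay with mortality, and the report must say so.

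Replacing the endpoints with ICU-free and hospital-free days to day 28 is less suitable here. It would change the endpoints after 191 patients had been recruited, and it may need post-discharge data that the Data collection section does not show. It would also largely repeat mortality: with 50% deaths and a survivor median of 18 days, about 0.50 + 0.50 × 0.26 = 63% of patients would score zero.

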### Sample size calculation

The sample size was calculated using PASS software (version 11, Kayesville, Utah, United States), based on several assumptions. The study by Hermite *et al*. [41] compared the event-free survival of catheters with citrate locks versus saline solution in ICU patients with an indication for extracorporeal RRT. In this study, the median duration of catheter survival with citrate locking solution was 12 days (interquartile range (IQR): 8 to 17], versus six days [3–10] for catheters locked with saline solution (hazard ratio (HR): 2.12, 95% confidence interval (CI): 1.32 to 3.4), *P* = 0.0019). The study by Weijmer *et al*. [15] reported an RR of 0.69 (95%CI: 0.44 to 1.08), *P* = 0.11) for premature withdrawal of non-tunneled, uncuffed catheters with citrate versus heparin. On the basis of these findings, in the prudent hypothesis of a reduction of 25% in the risk of catheter-related events (median of 12 days in the citrate group versus nine days in the heparin group), at an alpha risk of 5% and a beta risk of 20%, a total of 366 patients (183 per group) is required. Accounting for possible crossovers between groups (less than 5% switching from heparin to citrate) due to heparin-induced thrombocytopenia, and allowing for patients lost to follow-up, the final sample size is calculated to be 386 patients (193 patients included per group).

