To the best of our knowledge, only one randomized study, which included 291 patients, has compared the safety and efficacy of heparin versus citrate as a locking solution for non-tunneled catheters in hemodialysis patients [15]. The risk of catheter dysfunction was significantly lower in the citrate group, at 5 versus 8.1 events per 1,000 catheter days for citrate versus heparin respectively (relative risk (RR) 0.38, *P* = 0.015). The authors also noted a lower incidence of catheter infection in the citrate group (1.4 out of 1,000 catheter days) as compared to the heparin group (3.9 out of 1,000 catheter days) (RR 0.36, 95%CI 0.13 to 1.00, *P* = 0.05). Furthermore, the risk of bleeding and death from catheter-related bacteremia was significantly lower in the citrate group. Indeed, it should be noted that this study was prematurely interrupted because of a significant difference in catheter-related bacteremia between groups, in favor of the citrate group. Nevertheless, in this same study, the citrate concentration used was 30% (instead of 4%), and patients in intensive or critical care were excluded.

The primary objective of our study is to demonstrate the superiority of trisodium citrate 4% over heparin as a catheter lock solution, in terms of event-free survival of the first non-tunneled hemodialysis catheter inserted in patients hospitalized in intensive or critical care for AKI requiring extracorporeal RRT. Secondary objectives are to compare the rate of fibrinolysis, incidence of catheter thrombosis and catheter-related infection per 1,000 catheter days, length of stay in an ICU, and in-hospital and 28-day mortality.

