In the ICU setting, there are a number of different definitions of dialysis catheter dysfunction, and almost all are applicable in patients on intermittent RRT [41, 44]. In clinical practice, temporary dialysis catheter dysfunction can be defined as the failure to attain and maintain blood flow through the dialysis catheter sufficient for the administration of an adequate RRT dose [45]. Dysfunctions of this type can give rise to infectious complications [46, 47] and may even require that the catheter be changed. In the literature, the incidence of dysfunction depends largely on the type of catheter being used, its size, the anti-thrombotic catheter lock, the patient’s characteristics, the type of therapy and catheter maintenance [48]. In a study by Hryszko *et al*., the frequency of catheter dysfunction was 31.5% [44]. In the French Cathedia study, when only first dialysis catheter placement was assessed, the rate of dysfunction was 10.7% [49].

Infection of the dialysis catheter is a major challenge and can be responsible for 50 to 70% of catheter withdrawals [15, 36]. The incidence of infectious complications in dialysis catheters varies between reports, depending on the catheter type and the population studied. However, it is estimated that the incidence of catheter-related infections (including local infection and bacteremia) is between two and 14 events per 1,000 catheter days, with a median of six [15, 41, 49]. Repeated handling and catheter replacement over a metal guide in case of dysfunction increases the risk of infection [46, 47]. Catheter-related infections are associated with increased length of stay, increased risk of death and higher cost of care [50, 51]. Infections can be prevented by the strict respect of aseptic conditions at the time of catheter insertion.

A limitation of our study is that no analysis of the costs related to the use of citrate as a catheter lock solution (such as cost-efficacy, cost-effectiveness, absolute costs) is planned. Our working hypothesis is that trisodium citrate 4% will be shown to be superior to heparin in terms of risk of catheter dysfunction in non-tunneled hemodialysis catheters. The potential implications of this study are clearly important in the fields of critical and intensive care.

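### The 80% power claim leaves no stated room for censoring: at a hazard ratio of 0.75 a two-sided log-rank test needs about 380 events, which 386 patients give only if almost none are censored

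*Protocol article*

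**What the plan says.** In the protocol article, *Sample size calculation* sets the effect "in the prudent hypothesis of a reduction of 25% in the risk of catheter-related events", expressed as medians of 12 days with citrate and 9 days with heparin. It then states that "at an alpha risk of 5% and a beta risk of 20%, a total of 366 patients (183 per group) is required". The only inflation named is for loss to follow-up and "possible crossovers between groups (less than 5% switching from heparin to citrate"), which takes the total to 386 (193 per group). The section gives no required number of events and no expected event proportion. It does not say whether the 5% is one-sided or two-sided.

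*Primary objective* (statistical analysis) specifies a log-rank test on time from randomization to withdrawal of the first catheter, and adds: "Patients will be censored in case of scheduled withdrawal of the catheter, or death".

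*Background* says that ICU mortality "can reach 50 to 60% in patients with AKI".

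**The concern.** The information in a log-rank comparison comes from uncensored events. A patient whose catheter is removed as planned, or who dies with it in place, adds time at risk but no event. Both outcomes should be common in critically ill patients with acute kidney injury: some recover renal function and no longer need the catheter, and some die. If the patient count is about the same as the required event count, the design has no margin for either.

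What is at stake is how the result is read. A non-significant finding from a trial described as having 80% power for a 25% reduction would count as fairly strong evidence against a benefit of that size. If the real power is materially lower, that reading is too strong.

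**Working it through.** **Inputs, all from the article.** Medians 12 and 9 days, so the hazard ratio under exponential survival is 9/12 = 0.75, with ln 0.75 = −0.2877. Allocation 1:1. Alpha 5%, beta 20%. Log-rank test. The interim look uses alpha 0.0001, which has a negligible effect on the final test.

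**Attempt to reproduce 366.** With two-sided 5% and every patient followed to an event:

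- Schoenfeld: 4 × (1.960 + 0.842)² / (0.2877)² = 379.4, so 380 events.
- Freedman: 7.849 × (1.75/0.25)² = 384.6, so 385 events.
- Exponential hazard-difference formula: 387. Lakatos-type calculation: about 384.

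None of these gives 366. The nearest, 380, is 3.8% higher. The inflation step does reproduce: 366/0.95 = 385.3, which rounds up to 386 with equal groups.

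**Power if every patient has an event.** Power = Φ(√(d/4) × 0.2877 − 1.960), where d is the number of events.

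- d = 366: 78.6%
- d = 386: 80.7%

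So 80% is reached only with about 380 of 386 patients (98%) having an uncensored event.

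**Power with censoring.** The event proportion is not in the article. The proportions below are assumptions, with N = 386 and a two-sided test.

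| Assumed proportion with an uncensored event | Events | Power at HR 0.75 |
|---|---|---|
| 100% | 386 | 80.7% |
| 90% | 347 | 76.5% |
| 80% | 309 | 71.5% |
| 70% | 270 | 65.7% |
| 60% | 232 | 59.1% |
| 50% | 193 | 51.5% |

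With 193 events, the hazard ratio detectable at 80% power is exp(−2 × 2.802/√193) = exp(−0.403) = 0.67.

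**One-sided 5%.** 4 × (1.645 + 0.842)² / (0.2877)² gives 299 events. 299/386 = 77% of the patients would still need an uncensored event.

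**Crossover.** Under intention to treat, a heparin patient switched to citrate stays in the heparin arm and dilutes the effect. The hazards are ln 2/9 = 0.0770 and ln 2/12 = 0.0578 per day. With the full 5% switching, taken as on citrate throughout, the hazard ratio becomes 0.0578/(0.95 × 0.0770 + 0.05 × 0.0578) = 0.76. The effect is small, but it acts through the hazard ratio, not through the number of patients.

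**The case against.** The strongest reply is that the article condenses a fuller protocol, and the software inputs may have been reasonable. A one-sided 5% test with an assumed 28-day cut-off and exponential medians gives 355 (Schoenfeld) or 360 (Freedman) patients, which is close to 366 and has an event fraction below 100%. This stands as a possible origin, and for that reason a reader should not infer that 366 came from treating each patient as an event: that route gives 380 to 387. It does not rescue the claim, because neither assumption is stated and the route still leaves nothing for death or scheduled removal.

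It is also fair to say that the gap between 366 and 380 is minor in itself. It is; the missing allowance for censoring is what matters.

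Several stronger readings are tempting, but the article does not support them:

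- **A very low event rate.** *Background* cites "5 versus 8.1 events per 1,000 catheter days for citrate versus heparin respectively" for dysfunction, and *Discussion* cites a study in which, "when only first dialysis catheter placement was assessed, the rate of dysfunction was 10.7"%. One might project very few events from these figures. The first study excluded intensive and critical care patients and used 30% citrate. Dysfunction, even with infection added, is narrower than the primary endpoint, which also counts leakage, deterioration and accidental removal. *Discussion* also cites a dysfunction frequency of 31.5% elsewhere.
- **Planning medians that are really total dwell times.** The article describes the source of the 12-day median as a comparison of event-free catheter survival. Settling this would need that source.
- **A specific event count or an even chance of success.** The mortality figure is an upper value with no time horizon, and not every death occurs with the first catheter still in place. The article gives no rate of scheduled withdrawal. The 51.5% above is one row of a table, not an estimate.
- **An inflation wholly used up by crossover.** Crossover is put below 5% and in one direction, so fewer than 10 of 193 heparin patients, while 20 patients were added.

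**Conclusion.** The point holds. At a hazard ratio of 0.75 and two-sided 5%, 80% power needs about 380 to 385 events. The plan enrols 386 patients, censors scheduled withdrawal and death, and states no allowance for that censoring, so any material censoring leaves the stated power undelivered. The direction follows from the article's own figures and censoring rule.

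The size does not, because no event proportion is given. Under assumed proportions of 90% down to 50%, power runs from 76.5% to 51.5%. The figures rest on proportional hazards, the stated medians and a two-sided test. If the test is one-sided, the requirement falls to about 299 events, and the claim then depends on at least 77% of patients having an uncensored event, which the article does not assert.

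**What to change.** Restate *Sample size calculation* in events:

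1. State the sidedness of the 5% level and the required events: about 380 uncensored, unscheduled withdrawals for 80% power at a hazard ratio of 0.75, two-sided.
2. State an expected event proportion and its basis. The blinded pooled proportion among the patients already recruited (191 when the article was submitted) would serve.
3. Restate the power, or the detectable hazard ratio, that 386 patients deliver at that proportion.
4. Treat heparin-to-citrate crossover as a dilution of the effect (0.75 to about 0.76 at 5%), and keep loss to follow-up as a separate allowance.

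The cost is some rewording and one blinded event count, and the stated power becomes less favourable. This corrects the claim without restoring the power. Holding 80% would take about 380/0.80 = 475 patients at 80% events or 380/0.50 = 760 at 50%; whether to extend is a separate decision for the sponsor.
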